## 2. Materials and methods

### 2.1. Study design

The STRAIN study protocol was pre-registered at ClinicalTrials.gov (NCT06892977) and reported in accordance with the Strengthening the Reporting of Observational Studies in Epidemiology (STROBE) statement [23]. Recruitment for this study commenced on 8 February 2025 and is anticipated to conclude by 1 June 2026. Study completion and the release of initial results are expected by 1 December 2026. The study consists of a cross-sectional arm and a longitudinal arm (i.e., follow up at six months). A total of 140 participants will be recruited for this study, across four groups (n = 35/group): (1) a group with chronic widespread MSK pain (i.e., fibromyalgia), (2) a group with chronic localized MSK pain (i.e., non-specific low back pain (LBP) for ≥six months), (3) a group with subacute localized MSK pain (i.e., non-specific LBP for <three months), and (4) a pain-free control group (no history of chronic pain or current pain). All groups will participate in the cross-sectional arm which consists of a four-hour lab assessment at Ghent University (Ghent, Belgium) and three (consecutive) days of home assessments. Participants of the localized MSK pain groups will also participate in the longitudinal arm consisting of the same assessments, supplemented with assessing pain persistence or recovery. The study will be performed in accordance with the Code of Ethics of the World Medical Association (Declaration of Helsinki) and the international ethical and scientific quality standards accepted by the International Conference on Harmonization guidelines for Good Clinical Practice. Several patient-groups were involved in various stages of developing the study protocol, providing insights into the research and helping to minimize participant burden. The study protocol and data management plan were approved by the Medical Ethics Committee of Ghent University/Ghent University Hospital and all participants will provide written informed consent prior to study participation.

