### 2.10. Statistical analysis

A sample size calculation was performed using G*Power 3.1. A medium effect size was taken as a conservative omnibus estimation in relation to the stress assessments, based on previous studies. Large to very large effects have been observed for chronic stress [66] and basal cortisol levels [53]. Furthermore, acute stress inductions often failed to yield reliable cortisol responses, but medium to large effects have been observed for stress reactivity associations with self-reported pain responses [22].

Based on a one-way omnibus ANOVA (similar, but slightly more conservative than mixed linear models) with four groups, α of.05, desired power of.80, and a medium effect size of f = .30, 128 participants in total (n = 32 across four groups) are required. Accounting for corrupt or missing data, a sample of n = 35/group will be recruited. Additional sensitivity analyses were executed to calculate the observable effect size based on this sample in the longitudinal arm of the study (parameters: α = .05, power = .80, two groups, two measurements, correlation among repeated measures.2−.6; total sample n = 56 to account for 20% dropout/loss to follow-up). The calculation indicated that small to medium effects would be detectable (f = .17−.24) for within-between interactions in a repeated measures ANOVA.

The different outcome measures will be compared between participant groups and between different time points, using appropriate statistical tests (e.g., linear mixed model, ANOVA). Correlation analysis will be used to examine pain-stress interactions. For the longitudinal arm, analyses will focus on changes over time (i.e., baseline versus six-month follow-up), group comparisons based on pain status (i.e., recovered vs persisting) at follow-up, and interactions between changes over time in stress system functioning and the pain groups. At its core will be a linear mixed model analysis with ‘time’ as the within-subjects factor and ‘pain status group’ as the between-subjects factor. Post-hoc comparisons and adjustments for multiple comparisons will be made using Bonferroni-correction, unless more suitable post-hoc tests are identified. For all statistical tests, statistical significance will be accepted at an α of.05.

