### 2.11. General hypotheses

It is hypothesized that the pain groups that vary in pain extent and duration will show distinct profiles of stress system functioning. We expect that individuals with chronic widespread pain (fibromyalgia) will exhibit the most pronounced dysregulation of the stress system, characterized by lower basal cortisol levels due to chronic HPA axis exhaustion, blunted acute stress reactivity, prolonged stress recovery, increased ANS dysfunction with elevated sympathetic tone and reduced parasympathetic reactivation, and greater alterations in cortico-limbic circuitry, which will be associated with amplified pain sensitivity and impaired pain inhibition. Individuals with chronic localized LBP are expected to exhibit moderately dysregulated stress responses, with a mix of heightened and blunted HPA axis reactivity depending on pain extent and duration, increased basal stress levels as reflected in higher cortisol concentrations compared to pain-free controls, mild-to-moderate disruptions in ANS regulation, potentially less severe than in fibromyalgia and associated with impaired pain modulation. Individuals with subacute localized LBP are expected to display a more intact but still altered stress response compared to chronic pain groups, with heightened stress reactivity but preserved recovery, and increased risk for pain chronification (i.e., pain persistence at the six month follow-up) if they exhibit persistent stress exposure, higher basal stress levels, blunted stress reactivity, slower recovery, stress-induced hyperalgesia, and/or alterations in cortico-limbic circuitry. Pain-free individuals are hypothesized to exhibit a balanced stress response, with adequate stress reactivity and efficient recovery from acute stress induction, and the effective endogenous pain modulation compared to all pain groups.

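### Post-hoc comparisons use single-step Bonferroni, which a step-down procedure improves on at the same family-wise error, and the clause allowing another test sets no criterion or time for a switch

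*Protocol article*

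**What the plan says.** All of this is in section 2.10 of the protocol article unless noted.

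- Multiplicity: "Post-hoc comparisons and adjustments for multiple comparisons will be made using Bonferroni-correction, unless more suitable post-hoc tests are identified".
- Level: "For all statistical tests, statistical significance will be accepted at an α of.05".
- Sample size, from an omnibus test only: "with four groups, α of.05, desired power of.80, and a medium effect size of f = .30, 128 participants in total", raised for losses: "Accounting for corrupt or missing data, a sample of n = 35/group will be recruited".
- Section 2.11 expects that "the pain groups that vary in pain extent and duration will show distinct profiles of stress system functioning", and goes on to order the groups: fibromyalgia most dysregulated, chronic low back pain moderately so, subacute low back pain more intact, controls balanced.

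The section does not say which comparisons form a family (all pairs, each pain group against controls, time points or outcomes). It gives no power for any pairwise comparison, and does not say whether post-hoc tests depend on a significant omnibus result.

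**The concern.** The scientific questions concern pain extent and pain duration, and contrasts between particular groups answer them. A significant four-group omnibus test does not say which groups differ. The sample size protects only that omnibus test, so the efficiency of the pairwise step matters.

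Two features of the sentence work against this. First, single-step Bonferroni over six pairs tests every pair at .05/6 = .0083, however many pairs have already been rejected. Step-down procedures relax the threshold as rejections accumulate and still control family-wise error at .05. Second, the clause after the comma lets the procedure be replaced, with no rule for when or why. A family-wise error statement holds for a procedure fixed beforehand; here it is not fixed.

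**Working it through.** **Inputs from the article.** Four groups, α = .05, f = .30, N = 128 required (32 per group), 35 per group recruited (140 in total).

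**Assumptions, not in the article.** The family is all six pairs (4 × 3 / 2 = 6); pairwise tests are two-sided t tests with pooled variance on 4 × 34 = 136 degrees of freedom; outcomes are normal with SD 1; the mean patterns are those below.

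**1. The stated sample size.** Noncentral F with λ = f² × N and degrees of freedom 3 and N − 4:
- N = 124: power .796
- N = 128: λ = .09 × 128 = 11.52, power .810
- N = 140: λ = .09 × 140 = 12.6, power .85

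So 128 is the smallest equal-group total that reaches .80, and the article's figure reproduces.

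**2. Why dividing by six throughout is too strict.** Pairwise nulls among four means are logically linked. The number that can be true together is 6 (all means equal), 3 (three equal), 2 (two equal pairs), 1 or 0. Once one pair has been rejected, at most three of the rest can be true. Shaffer's divisors are therefore 6, 3, 3, 3, 2, 1. If a significant omnibus F has already rejected equality of all four means, they become 3, 3, 3, 3, 2, 1. Holm ignores this structure and uses 6, 5, 4, 3, 2, 1.

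**3. Mean patterns scaled to f = .30.** Here f is the SD of the four means.
- One group differs from three: f = d√3/4, so d = .30 × 4/√3 = 0.69 SD.
- Two groups against two: f = d/2, so d = 0.60 SD.
- Equally spaced means: f = s√1.25, so the step s = 0.27 SD, two steps 0.54 SD, three steps 0.80 SD.

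**4. Average power per true difference** (simulation, 35 per group, 100,000 runs per pattern):

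| Pattern | Bonferroni | Holm | Shaffer | Omnibus-gated Shaffer |
|---|---|---|---|---|
| One vs three | .589 | .619 | .656 | .669 |
| Two vs two | .437 | .479 | .510 | .530 |
| Equally spaced | .269 | .294 | .318 | .325 |

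Gain over Bonferroni, in percentage points, in the same row order:
- Holm: 3.0, 4.2, 2.5
- Shaffer: 6.7, 7.3, 4.9
- Omnibus-gated Shaffer: 8.0, 9.3, 5.6

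As a ratio, gated Shaffer finds .669/.589 = 1.14, .530/.437 = 1.21 and .325/.269 = 1.21 times as many true differences.

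**5. Inside the equally spaced pattern.** Bonferroni to gated Shaffer: one-step pairs about 6% to 10%, two-step pairs 33.6% to 42.7%, the three-step pair 75.5% to 79.7%. The gain of about 9 points belongs to two of the six pairs; the average over all six is 5.6.

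**6. Error control.** Simulated family-wise error with all means equal: .040 for Bonferroni, Holm and Shaffer, .047 for gated Shaffer. With one group different, gated Shaffer gives .043; with two against two, .033. All are within .05.

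**7. Does the replacement ever reject less?** Holm and ungated Shaffer never do: their thresholds are at least .05/6 at every step. Gated Shaffer can, when a pair passes .0083 but the omnibus F is not significant. That happened in under 1% of runs.

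**The case against.** Bonferroni is valid and conservative, and it gives simultaneous confidence intervals directly. The article promises no pairwise power, so no stated figure is wrong. This stands: the power part is about efficiency only.

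The family of six pairs is an assumption, and the gain depends on it. With three comparisons against controls, Holm gains between 0.1 and 6.0 points over Bonferroni, or about 7.7 if all three pain groups differ equally from controls. Shaffer's divisors also do not fit the longitudinal model, which has two pain-status groups and two measurements. This stands too, and it is why the fix uses Holm generally and Shaffer only for the six group pairs.

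A reader might infer that Bonferroni costs 8 to 9 points against any step-down method. The calculations do not support that. The figure belongs to omnibus-gated Shaffer when one group differs from three or two from two. Graded means, the pattern closest to section 2.11, gain about 5.6 points on average, and Holm gains only about 2 to 4.

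A reader might also infer that the test will be chosen after p-values are seen. The clause permits this but does not say it. A separate analysis plan, not shown, may settle procedure and timing. What remains is that the article names a method and, in the same sentence, allows its replacement without a criterion or a time point.

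**Conclusion.** The point holds as one of efficiency and pre-specification. Assuming six pairs, f = .30, 35 per group, two-sided tests and the patterns above, single-step Bonferroni gives up about 2 to 4 points of average power per true difference against Holm, about 5 to 7 against Shaffer and about 5.5 to 9 against omnibus-gated Shaffer. None of these exceeds .05 family-wise error. The sizes depend on the assumed family and means; that Holm and ungated Shaffer reject at least as much as Bonferroni does not. The open switching clause is a defect whatever the power figures. The documents do not show that error is inflated or that a data-driven choice is planned. The sample size of 128 is correct for the omnibus test it was computed for.

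**What to change.** Replace the sentence in section 2.10 with: *Post-hoc comparisons are adjusted by Holm's procedure within each stated family; for the six pairwise comparisons of the four groups, Shaffer's step-down procedure (divisors 6, 3, 3, 3, 2, 1, or 3, 3, 3, 3, 2, 1 after a significant omnibus test) is used.* State which of the two Shaffer versions applies and list the families. Delete the switching clause, or require any change of procedure to be fixed and documented before the data are analysed.

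This costs one sentence and no participants, visits or assays. Simultaneous confidence intervals are less direct under step-down testing; Bonferroni intervals can be reported alongside. If the gated version is chosen, a pair that Bonferroni alone would have declared will occasionally be lost, in under 1% of the simulated cases.

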### 2.11. General hypotheses

It is hypothesized that the pain groups that vary in pain extent and duration will show distinct profiles of stress system functioning. We expect that individuals with chronic widespread pain (fibromyalgia) will exhibit the most pronounced dysregulation of the stress system, characterized by lower basal cortisol levels due to chronic HPA axis exhaustion, blunted acute stress reactivity, prolonged stress recovery, increased ANS dysfunction with elevated sympathetic tone and reduced parasympathetic reactivation, and greater alterations in cortico-limbic circuitry, which will be associated with amplified pain sensitivity and impaired pain inhibition. Individuals with chronic localized LBP are expected to exhibit moderately dysregulated stress responses, with a mix of heightened and blunted HPA axis reactivity depending on pain extent and duration, increased basal stress levels as reflected in higher cortisol concentrations compared to pain-free controls, mild-to-moderate disruptions in ANS regulation, potentially less severe than in fibromyalgia and associated with impaired pain modulation. Individuals with subacute localized LBP are expected to display a more intact but still altered stress response compared to chronic pain groups, with heightened stress reactivity but preserved recovery, and increased risk for pain chronification (i.e., pain persistence at the six month follow-up) if they exhibit persistent stress exposure, higher basal stress levels, blunted stress reactivity, slower recovery, stress-induced hyperalgesia, and/or alterations in cortico-limbic circuitry. Pain-free individuals are hypothesized to exhibit a balanced stress response, with adequate stress reactivity and efficient recovery from acute stress induction, and the effective endogenous pain modulation compared to all pain groups.

## 3. Discussion

This study will be the first to comprehensively map the functioning of the stress systems (i.e., ANS and HPA axis) and investigate its relationship with pain sensitivity and modulation across groups categorized by pain duration and extent, as well as its role in pain recovery and chronification.

MSK pain, especially low back pain, is the primary cause of disability and affects more than half a billion people worldwide [67]. Given the limited understanding of the role of stress in the extent of pain symptomatology, its contribution to the risk of pain chronicity, and mechanisms underlying the interaction between stress and pain—coupled with the significant heterogeneity in the existing literature—this study aims to provide novel and critical insights into the psychosocial, (psycho)physiological and neural mechanisms underlying the stress-pain relationship. This is an indispensable prerequisite before we can take the next steps to examine and develop well-targeted and successful prevention strategies and treatments for acute and chronic MSK pain.
